#### The Flourishing Scale (FS)

The FS is an eight item self-report measure of psychological well-being [59]. The scale taps into aspects of human functioning such as feelings of competence, positive relationships, and purpose in life. It uses a 7-point Likert scale with responses from strong disagreement to strong agreement. Scores range from 8 to 56 and high scores indicate positive self-appraisal of psychological well-being. The scale developers report strong correlations with other psychological well-being scales and good internal consistency with Cronbach’s alpha coefficient of 0.87.

#### Mindfulness-based Self-Efficacy Scale-Revised (MSES–R)

This 22-item self-report measure is designed to assess the changes in levels of perceived self-efficacy before, during and after mindfulness-based therapy [32]. There are six subscales, Emotion Regulation, Distress Tolerance, Equanimity (considered here as measuring aspects of equanimity), Taking Responsibility, Social Skills, and Interpersonal Effectiveness (considered here as measuring aspects of interpersonal skills). Items are rated on a 5-point Likert scale from 0 (*not at all*) to 4 (*completely*). Higher scores indicate higher mindfulness based self-efficacy. Subscales can be used separately to assist in identifying relative strengths and weaknesses or combined to provide a global score. The MSES-R total shows high internal consistency (Cronbach’s alpha .86) [32]; has a good divergent validity, inverse relationships with the DASS-21 [60], and good concurrent validity with the Freiberg Mindfulness Inventory (FMI) [61], the Mindfulness Attention and Awareness Scale (MAAS), [62], the Kentucky Inventory of Mindfulness (KIMS), [63, 64] and the Five Factor Mindfulness Questionnaire (FFMQ), [65, 66].

#### The Experiences Questionnaire (EQ)

This is a 20-item self-report measure of decentring [67] and is conceptualized as a protective factor and capable of measuring resilience to depressive relapse. Decentring is a key element of metacognitive awareness [68, 69] as reflected here: “We refer to the process of experiencing negative thoughts and feelings within a decentred perspective as metacognitive awareness..” [70]. The EQ uses a 5-point Likert scale with responses from “never” to “all the time”. This is a relatively new measure whose psychometric properties are still being investigated. A Spanish study [71] found (reliability: Cronbach’s α = .89; convergent validity: r > .46; and divergent validity: r < − .35).

#### Multi-dimensional Assessment of Interoceptive Awareness (MAIA)

This is a 32-item self-report measure of body awareness, both interoceptive and proprioceptive [44]. It uses a 6-point Likert scale with responses from 0 (never) to 5 (always). There are eight subscales; Noticing, Not-Distracting, Not-Worrying, Attention Regulation, Emotional Awareness, Self-Regulation, Body Awareness and Trusting [44]. The internal-consistency reliability of each of the 21 validity measures was reported by the scale developers as ranging from .70 to .93 (median .85) [44, 72].

#### The Nonattachment Scale (NAS)

This unidimensional measure is designed to tap the construct of being equanimous, flexible and receptive [73]. This appears to be congruent with cognitive flexibility, an attribute that is developed by mindfulness practice. The NAS is shown to correlate with a quality of consciousness related to constructs such as emotion regulation, interpersonal effectiveness, well-being and mental health [73]. It is a 30-item self-report scale and uses a 6-point Likert scale ranging from 1 (disagree strongly) to 6 (agree strongly). Internal consistency levels are >.80 (Cronbach’s alpha).

#### Meditation practice

The amount of meditation practice completed by each participant is recorded daily by each participant and then collected each week on an individualized form. They are not disclosed to other participants.

#### Adverse effects

There is a weekly check in with participants about their practice and any issues raised are addressed. In the event of participants experiencing difficulties in relation to their meditation practice the following actions may be taken: a) modify the type of practice for the coming week or b) provide some individual counselling to the participant. The 6-month follow-up questionnaire includes a question about the occurrence of any adverse effects or other difficulties thought to be as a result of meditating. The questions were taken from a recent study about the broad ranges of experiences that occur in association with meditation practices [74]. The questions are:
“Did you have any unexpected, challenging, or difficult experiences that you associate with your practice of meditation?”“How did these experiences impact your life”? [74].

All measures will be administered on line using Qualtrics survey software, with the exception of the amount of meditation practice which will be recorded by each participant and reported privately on a personalized form each week. There are inadequate resources available for this PhD study to administer the qualitative questions in person.

Participants are emailed a link to the measures utlizing their unique identification number. Reminder emails are sent to those who do not respond and if there is still no response the participant is telephoned.

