### Intervention

The MiCBT intervention is adapted from the published protocol [32] with the variation that individual sessions between each group session are not be routinely offered; such sessions are only offered to a participant if a crisis emerges that is deemed too complex to address in a group situation. The MiCBT group will receive the MiCBT treatment in a group format comprising weekly two-hour sessions to groups of 10–15 participants for 8 weeks. The program is delivered by one MiCBT-trained psychologist with 9 years of experience in delivering MiCBT, including twenty-five MiCBT groups. The intervention is administered in a psychology clinic. Participants will be asked to engage in specific mindfulness meditation for an hour each day; two half hour practice sessions and are asked to log their meditation practice hours. Audio instructions for the mindfulness exercises for each session are provided from Cayoun’s (2015) text (used with permission). At the start of each session there is a facilitated group meditation for half an hour which introduces the meditation practice for the following week. There is a review and inquiry process about the experiences of the previous weeks practice and in the second hour of each session there is a psycho-educational component explaining the rationale for the following weeks practice or introducing specific homework designed to apply the skills acquired (e.g. an exposure task to avoided behaviors). Attendance at each session is recorded and non-attenders are followed up. Figure 3 maps the putative processes and outcomes in MiCBT.

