### Sample size

The trial is powered to detect significant differences relevant to the primary outcome. A power analysis (G-power 3.1) for medium effect (Cohen’s d = .5) was conducted with power of .08, and using the conventional significance level (.05), resulting in a desired sample of 102 (51 participants in each group). Consistent with previous studies (e.g. [75]) allowing for a conservatively estimated attrition rate of 20% to follow up, a sample of 120 will be recruited. Based on the projected sample size of 102, power of 0.8, and zero, small, medium or large effect sizes conditions for the indirect effect, the mediation analyses are well-powered to detect a medium beta paths between the independent variable and the mediator and between the mediator and the dependent variable (β = .0.39) using bootstrapping and the Sobel test [76]. Data will be collected using online self-report measures with the Qualtrics platform at the four measurement points; baseline, mid-intervention, post-intervention, and 6-months follow-up.

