### Data collection

In addition to the quantitative measures previously described participants in the MiCBT group will be asked some additional qualitative questions at the end of the 8-week program evaluating the program and asking about any adverse events they may experience with their meditation practices during the MiCBT program. Additionally, at the 6-month follow up, participants in the MiCBT group will be asked questions relating to adherence to meditation practices and any changes to treatment. Participants in the control condition will complete all measures at the same four time points as the treatment group and receive treatment as usual during this time.

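### As described, harm data come only from retrospective online questions to the MiCBT group; difficulties raised at weekly check-ins are handled but not recorded as data, so harms in non-responders may be under-recorded

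*Protocol article*

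**What the plan says.** The Adverse effects section describes a live response to difficulties: "There is a weekly check in with participants about their practice and any issues raised are addressed". Where meditation causes difficulty, the facilitator may "a) modify the type of practice for the coming week or b) provide some individual counselling to the participant". The same section then names one point at which harm is asked: "The 6-month follow-up questionnaire includes a question about the occurrence of any adverse effects or other difficulties thought to be as a result of meditating". It prints two open questions for this purpose. It adds that all measures are completed online except the amount of practice, which goes on a personal weekly form, and that resources do not allow the qualitative questions to be put in person. The Blindness section repeats that everything other than practice data is collected online.

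The Data collection section names a different point: "participants in the MiCBT group will be asked some additional qualitative questions at the end of the 8-week program", including a question on adverse events during the program. For 6 months it says that the same group "will be asked questions relating to adherence to meditation practices and any changes to treatment", with no mention of a harm question.

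Three other statements bear on who will be reached. The Intervention section says "Attendance at each session is recorded and non-attenders are followed up". The Adverse effects section says that questionnaire non-responders are reminded by email and then telephoned. The Sample size section sets the recruitment target by "allowing for a conservatively estimated attrition rate of 20% to follow up".

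**The concern.** The weekly check-in is the one place where a difficulty is seen close to when it happens. As described, it leads to an action but not to a record. The harm result then depends on a questionnaire being returned later.

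Take a participant who is distressed in week 3, is counselled, stops in week 4 and answers neither later questionnaire. On the description given, that person leaves an attendance record and perhaps some practice hours, but no harm record. If people made worse by the practice are also less likely to answer, the reported harm rate will be too low.

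The split description adds uncertainty. A reader of the Adverse effects section alone would plan for a 6-month harm item; a reader of the Data collection section alone would plan for a week-8 item. The printed 6-month questions set no time window, so it is unclear whether they would repeat, or add to, what was reported at week 8.

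**Working it through.** No stated figure is in dispute, so the check is a comparison of the text followed by arithmetic for scale.

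**Sources of harm information as described**

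| Point | What happens | Described as data? |
|---|---|---|
| Weekly check-in (Adverse effects) | Issues addressed; practice modified or counselling given | No |
| Weekly form (Meditation practice; Adverse effects) | Amount of practice | Yes, but no harm content described |
| Attendance (Intervention) | Recorded; non-attenders contacted | Attendance yes; no harm question described |
| Week 8 (Data collection) | Adverse events during the program, MiCBT group | Yes |
| 6 months (Adverse effects) | Adverse effects or difficulties attributed to meditating | Yes |
| 6 months (Data collection) | Adherence and changes to treatment | Yes; harm not listed |

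Nothing in the two 6-month rows is exclusive. One section says what the questionnaire includes; the other introduces its 6-month questions as an addition. Asking at both times fits both sections.

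**How many could be missing at 6 months**

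Inputs: 120 recruited and 20% attrition (Sample size section); equal allocation is assumed, giving 60 per arm, and the same attrition is assumed in each arm.

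- No 6-month answer: 60 × 0.20 = 12
- Responders: 60 − 12 = 48

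The 20% refers to follow-up. The documents give no non-response rate for week 8.

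**What that could do to the harm rate**

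The documents give no harm rate, so the true rate *h* and the non-response *q* among those harmed are assumptions. The calculation treats one questionnaire as the only source.

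- Harms unrecorded = 60 × *h* × *q*
- Apparent rate = 60 × *h* × (1 − *q*) / 48

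With *h* = 10%, there are 6 true harms in 60:

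| *q* | Unrecorded | Recorded | Apparent rate |
|---|---|---|---|
| 20% | 1.2 | 4.8 | 4.8/48 = 10% |
| 40% | 2.4 | 3.6 | 3.6/48 = 7.5% |
| 60% | 3.6 | 2.4 | 2.4/48 = 5% |

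For *h* from 5% to 20% and *q* from 20% to 60%, the unrecorded number runs from 60 × 0.05 × 0.20 = 0.6 to 60 × 0.20 × 0.60 = 7.2.

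If harmed participants fail to answer at the same 20% as everyone else, events are missed but the rate among responders is unbiased. If they fail to answer at 60%, the reported rate is half the true one. An answer at week 8 from someone missing at 6 months would reduce the loss of program-period harms.

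**The case against.** The strongest reply is that the plan already asks about harm twice and pursues those who do not answer. Much of this stands, and it rules out several stronger readings.

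- **That the two sections contradict each other.** A reader might infer this because each names a different time. Neither says that its question is the only one, and asking at both times satisfies both.
- **That an early reaction is recalled only 7 to 8 months later.** This needs a harm question at 6 months alone. With the week-8 question, a week-2 reaction is asked about some 6 weeks later.
- **That harms in people who stop early are lost.** Stopping sessions is not leaving data collection. The week-8 questions go to the MiCBT group, not to completers; non-attenders are followed up and silent participants are telephoned. Only those who still do not answer would be missed.
- **That harm is understated by about 40%.** Such a figure comes from assuming harm in 5–10% of responders and 25–40% of non-responders: (48 × 0.05 + 12 × 0.25)/60 = 9% against 5% reported, or (48 × 0.10 + 12 × 0.40)/60 = 16% against 10%. No figure in the documents supports that difference.

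It can also be said that adverse-event forms and the content of follow-up calls are details that an article leaves to the full protocol. That is fair, and the absence of a log from the article is not itself an error. But the article goes further than silence: it states that practice amount is the only measure collected outside the online system, and that the qualitative questions cannot be asked in person. On that wording the weekly check-in is not a data source, and the telephone call cannot be assumed to collect the harm answers.

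**Conclusion.** The concern holds as a limited weakness in how harms are ascertained. As described, harm data rest on retrospective online questions, real-time difficulties are not captured as data, and the two time points are never stated together. Harms in MiCBT participants who answer neither questionnaire may be under-recorded.

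The size is bounded but not known. Up to about 12 of 60 MiCBT participants would give no 6-month answer, assuming equal allocation and the planned 20% attrition in that arm. The number silent at both week 8 and 6 months cannot be derived. The bias in the harm rate could be nil or, under the assumed range above, as much as a halving. The efficacy analysis is not affected.

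**What to change.** 1. State in both the Adverse effects and Data collection sections that the harm item is asked at week 8 and at 6 months, and the period each covers: for example, weeks 1–8, then the time since week 8.
2. Log any difficulty raised at the weekly check-in, and the action taken, on the weekly form already collected.
3. Ask the harm item and the reason for stopping when non-attenders are followed up, and ask the harm item when questionnaire non-responders are telephoned.
4. Report harms over all MiCBT participants who started, combining these sources, and state how many have no harm information from any of them.

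The cost is one line on an existing form, a short question at contacts already made, and one item in two existing surveys. The downside is slightly more recording by the facilitator and possibly a less favourable harm rate. The change concerns recording and reporting only; no change to clinical management is proposed.

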**Fig. 2 Fig2:**
[figure not shown]
Co-emergence model in disequilibrium

The MiCBT program structure (depicted in Fig. 3) is designed to systematically develop skills to achieve this rebalancing process. Stage 1 (weeks 1–3) teaches mindfulness meditations, both breath meditation and body scanning to develop attention regulation, metacognitive and interoceptive awareness together with response inhibition or non-reactivity/equanimity. Stage 2 (weeks 4–5) further develops interoceptive awareness, teaching the first body scan in a series of advanced and systematic scanning methods to enable sensitivity to even very subtle body sensations in all areas of the body, followed by imaginal and in vivo exposure techniques for managing avoidance. Stage 3 (week 6) uses faster body scanning techniques and uses exposure methods to address interpersonal issues and assertiveness. Stage 4 (weeks 7–8) teaches deeper levels of body scanning and introduces awareness of ethics and compassion for self and others. Increased awareness of, and equanimity towards, body sensations facilitates the introduction of behavior change strategies so that imaginal and in-vivo exposure to avoided situations (including interpersonal situations) becomes manageable. This practical technique positively impacts social functioning, enabling difficult avoided situations and conversations to be possible. The resultant improved social functioning and connectedness with others tends to enhance well-being and flourishing [33] and assist in preventing relapse [34]. The explicit practice of compassion and personal ethics as an aspect of psychological well-being, combined with the use of systematic exposure techniques, are features distinguishing MiCBT from other MBIs.

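### The adverse-effect questions are limited to meditation, so harm from MiCBT's exposure tasks is not systematically asked about

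*Protocol article*

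**What the plan says.** **Harm questions.** Under Measures, Adverse effects, the protocol article states: "The 6-month follow-up questionnaire includes a question about the occurrence of any adverse effects or other difficulties thought to be as a result of meditating". It prints the lead item, "Did you have any unexpected, challenging, or difficult experiences that you associate with your practice of meditation", and a second item that asks how those same experiences affected the participant's life. It says both were taken from a study of experiences associated with meditation. Under Data collection, the MiCBT group also gets qualitative questions at the end of the program, "evaluating the program and asking about any adverse events they may experience with their meditation practices during the MiCBT program".

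**Weekly contact.** The Adverse effects section adds: "There is a weekly check in with participants about their practice and any issues raised are addressed". The possible responses are to modify the practice or to provide individual counselling. Recording these contacts as harm data is not mentioned.

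**Content of the intervention.** The description of program structure in the Background places "imaginal and in vivo exposure techniques for managing avoidance" in Stage 2 (weeks 4–5). It says that Stage 3 (week 6) "uses exposure methods to address interpersonal issues and assertiveness". The same paragraph names systematic exposure among the features that set MiCBT apart from other mindfulness programs. The Intervention section gives an exposure task as its example of homework.

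**The concern.** MiCBT has several components, but the described harm enquiry covers only one of them. A participant who becomes distressed after confronting an avoided situation, or after a difficult assertive conversation, may not connect this with meditating and could answer the 6-month item in the negative in good faith. That item also leaves the causal attribution to the participant, so a deterioration put down to something else is not elicited by it.

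What is at stake is how an adverse-effect report from this trial would be read. A low count would naturally be taken to describe MiCBT as a whole, when the questions had asked about its meditation component. The Randomization section provides a stratum for K10 scores of 30 or more, so the sample is expected to include severely distressed patients.

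**Working it through.** No arithmetic applies: the document gives no adverse-event rate and no safety figure to reproduce. The check sets what is asked beside what is delivered.

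| Source of harm information | Section | Scope as described |
|---|---|---|
| Week-8 question, MiCBT group | Data collection | Adverse events with meditation practices, alongside general program evaluation |
| 6-month lead item | Adverse effects | Experiences associated with meditation practice |
| 6-month second item | Adverse effects | Impact of the experiences named in the lead item |
| Weekly check-in | Adverse effects | Practice; issues dealt with, recording not stated |
| Individual session in a crisis | Intervention | Not limited to meditation; recording not stated |

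| Component delivered | Section | Named in a harm question? |
|---|---|---|
| Breath meditation and body scanning | Background, program structure | Yes |
| Imaginal and in vivo exposure, Stage 2 | Background, program structure | No |
| Interpersonal exposure and assertiveness, Stage 3 | Background, program structure | No |
| Exposure task as homework | Intervention | No |

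**Could the word practice cover exposure?** The protocol's own usage points the other way. The Intervention section treats the coming week's practice and the applied homework as alternatives within the session's second hour, and its example of homework is an exposure task. The practice that participants log is meditation (Intervention; Meditation practice). The 6-month item says meditation outright.

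**Is this only a detail left to a fuller document?** Not for the 6-month item, whose wording is printed. The week-8 question is paraphrased, so its exact wording is unknown, but the paraphrase fixes its scope as meditation practices.

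**Direction.** A question about one component can miss events that arise from another and does not add any. The error is therefore towards under-counting relative to the whole program.

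**Size.** It would require the rate of exposure-related adverse experiences and the share of them that participants would not link to meditation. Neither is in the document, so no figure is offered.

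**The case against.** The case against has real force on several points.

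- **No safety conclusion is planned.** Aims and hypotheses, Primary and secondary outcomes, and Statistical analysis contain no tolerability objective, hypothesis or test. This stands. A reader might infer that a planned tolerability conclusion would come out too favourable; the protocol plans none. The point concerns only such adverse-effect statements as may be made.
- **Other routes exist.** The DASS-21 and K10 are collected mid-intervention, post-intervention and at 6 months, at the same time points in controls. The week-8 questions also evaluate the program generally, and the weekly check-in, follow-up of non-attenders and crisis sessions may bring problems to light. This stands against the inference that exposure-related harm goes unrecorded. It does not close the gap: the article does not say that these contacts are logged as harm data, and chance disclosure is not systematic enquiry.
- **Participants may attribute exposure distress to their practice.** The Background says that awareness of and equanimity towards body sensations make exposure manageable, so some may make that link. This stands in part and limits the loss by an unknown amount.
- **The wording was borrowed deliberately.** Keeping it preserves comparability with its source. This stands, and it argues for adding an item rather than replacing one.
- **Timing.** A reader might infer that Adverse effects and Data collection contradict each other on when harm is asked about. They read naturally as two complementary points, week 8 and 6 months. The 6-month list under Data collection is not said to be exhaustive.

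**Conclusion.** The point holds as a limited defect in measurement. The adverse-effect questions described, at week 8 and at 6 months, are confined to meditation, while exposure is a named and distinguishing part of the treatment. Exposure-related harm is not systematically asked about, and an adverse-effect statement about the whole program would rest on incomplete ascertainment.

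The direction is under-counting and the size is unknown. It would be tempting to size it by the share of program weeks that contain exposure, or by an upper confidence limit for zero reports. Neither works. Meditation continues through those weeks and is inside the question, and a confidence limit for zero events would be the same under a perfectly worded item.

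The conclusion assumes that the week-8 question has the scope its paraphrase gives it, and that at least some participants would not ascribe exposure distress to meditating. The planned primary, secondary and mediation analyses are untouched. This is a worthwhile improvement and not a threat to the trial's efficacy result.

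**What to change.** 1. At both existing time points, week 8 and 6 months, extend the enquiry to unexpected, challenging or difficult experiences linked to any part of the program, naming meditation, exposure tasks and interpersonal exercises. Either broaden the current question or, to keep comparability with the source study, leave the borrowed item as it is and place the broader one beside it.
2. Tabulate by arm the number of participants whose DASS-21 worsened from the pre-treatment value by more than a reliable-change amount fixed in advance, at mid-intervention and post-intervention. The data are already collected in both arms, and no attribution by the participant is needed. The total-scale reliability quoted in the DASS-21 section (.93), with the pre-treatment standard deviation, is enough to define that amount.
3. Until this is done, describe any adverse-effect result as relating to meditation practice and not to MiCBT as a whole.

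The cost is one extra questionnaire item or a slight departure from the published wording, one extra table, and possibly more events recorded. Allocation, treatment and the planned efficacy analyses do not change.
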